##### Sociodemographic, clinical information

We will collect participants’ sociodemographic (e.g., age, marital status, education level, professional status) and clinical (presence of medical diagnosis, actual medication, sensory issues, mobility deficits, use of substances, and previous issues and hospitalization) information through a questionnaire developed by the researchers. Biological markers of neurodegeneration will also be collected at the baseline and post-intervention.

##### Primary outcome

Given the multidomain nature of this intervention, we will consider as primary outcomes the following:A *cognitive function composite *(z-score) will be calculated from the total Mini Mental Status Exam (MMSE) score [53], Word List Total Recall Score (WMS-III) [54], Category Fluency total [55], and Trails Part B [56], providing a measure of global cognitive function.*Healthy lifestyle behaviors*, measured with Healthy Lifestyle Assessment Toolkit (HLAT) [57]. This will measure adherence to physical activity, cognitive engagement, and diet and will be complemented with qualitative interviews for a subsample of participants. These outcomes will be measured in all assessment time points (pre-, post-, 3-, 6-, and 18- months follow-up).

These outcomes will be measured in all assessment time points (pre-, post-, 3-, 6-, and 18- months follow-up).

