### Objectives

Therefore, our aims are:

Primary outcomes.

To test the efficacy of the REMINDER program in improving global cognition and protective lifestyle behaviors (e.g., physical activity, diet, social engagement, sleep hygiene, cognitive stimulantion, and regular health monitoring) in individuals at risk of dementia (community-dwelling or MCI) at immediate, short- and long-term follow-up.

Secondary outcomes.

To examine the efficacy of the REMINDER program on neuropsychological functioning, including emotional, cognitive, and functional domains;To evaluate the additive effect of including REMINDER4Carers to the REMINDER program on lifestyle behavior, cognition, and well-being of MCI patients;To examine the effects of the REMINDER program on markers of neurodegeneration (blood-based biomarkers and neuroimaging markers).

Exploratory outcome.

To monitor diagnostic transitions in the MCI subgroup (conversion to dementia) across the 18-month follow-up, and examine whether participation in REMINDER alone or and REMINDER with caregiver support may delay progression compared to the waiting list control.

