### Trials design

The study will assess the program’s efficacy in healthy at-risk individuals and those with MCI across community and clinical settings. To adress our research questions, this project employs two superiority randomized controlled trials (RCTs) running in parallel. The Community Trial targets at-risk healthy individuals (*N* = 270) and will be a three-arm, single-blind RCT with 1:1:1 randomization: (1) REMINDER face-to-face, (2) REMINDER virtual, and (3) waiting list control group without active intervention. The Clinical Trial targets individuals with MCI (*N* = 270) and will be a three-arm RCT with 1:1:1 randomization: (1) REMINDER alone, (2) REMINDER with caregiver support, and (3) waitlist control group.

We chose to investigate both community-dwelling at-risk individuals and patients with MCI in order to cover the continuum of cognitive decline prior to dementia, as both groups represent critical targets for prevention but remain underrepresented in multidomain intervention trials.

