#### Sample size

The sample size estimation was performed in “G*Power”, a statistical software program. Power analysis was performed and was based on both existing data on the effects of dementia risk reduction programs in a cognitive composite [28, 76] as well as in our preliminary feasibility study results that held small to medium effects (f >0.20). Accordingly, for the Community trial, a total sample size of 244 was determined based on an expected power of 0.80 to detect small to medium effects (f >0.20) in comparison analyses in the primary outcomes (e.g., cognitive composite; lifestyle change) (G*Power). Considering an expected dropout rate of 10%, a total sample size of 268 participants leads to an approximate required final expected sample size of 270 (90 per arm). For the Clinical Trial, the same power analysis was performed, and considering now three arms, a final sample size of 270 is distributed across arms, with 90 participants per arm.

Given the multifactorial higher risk of women developing dementia, we will take this into account in the sex/gender ratio of the sample recruited as well as in the efficacy analyses.

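### Two primary outcomes, three arms and every follow-up visit, but no decisive visit, contrast or success rule; the sample size fits a single test at 0.05

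*Protocol article*

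**What the plan says.** **Outcomes.** The Primary outcome section of the protocol article opens with "Given the multidomain nature of this intervention, we will consider as primary outcomes the following" and names two: a cognitive z-score composite and the HLAT lifestyle measure. It gives no rule for combining them.

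**Visits.** The same section adds "These outcomes will be measured in all assessment time points (pre-, post-, 3-, 6-, and 18- months follow-up". The primary aim under Objectives is efficacy "in individuals at risk of dementia (community-dwelling or MCI) at immediate, short- and long-term follow-up", with the horizons unranked.

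**Arms.** Under Trials design, the Community Trial is a "three-arm, single-blind RCT with 1:1:1 randomization: (1) REMINDER face-to-face, (2) REMINDER virtual, and (3) waiting list control group without active intervention". The Clinical Trial is a "three-arm RCT with 1:1:1 randomization: (1) REMINDER alone, (2) REMINDER with caregiver support, and (3) waitlist control group". Hypotheses compares REMINDER participants with the waitlist and does not say whether the active arms are pooled. The caregiver-support contrast is a secondary aim under Objectives, but Hypotheses ties it to the primary outcome, in the singular.

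**Control period.** Waiting list control groups limits the no-intervention comparison to the 6-month follow-up period. Participants says that the waitlist is offered the programme after 6 months.

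**Test and size.** Statistical methods names linear mixed models with a time-by-group interaction for primary and secondary outcomes alike. Sample size gives power 0.80 at f = 0.20, a total of 244, "in comparison analyses in the primary outcomes (e.g., cognitive composite; lifestyle change" among the endpoints covered, and then 268 and 270 after 10% dropout. No alpha is printed.

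**The concern.** Which outcome, visit and contrast decide the trial is core protocol content. The article addresses each of the three and leaves each open, so this is more than a detail that an analysis plan could be expected to supply.

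Two things are at stake. First, if either outcome, either active arm and any visit may support a claim, the chance of a false one exceeds 5%. Second, if the error rate is controlled by splitting alpha, the stated power no longer holds for the test used to size the trial. In addition, the long-term part of the primary aim rests on a visit at which the control group may already have had the programme.

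**Working it through.** **1. Reproduce the stated N.** For a one-way F test with 3 groups, df = (2, N − 3) and noncentrality λ = N·f². With f = 0.20 and N = 244, λ = 244 × 0.04 = 9.76. At alpha 0.05 the power is 0.8002, and 244 is the smallest N reaching 0.80. At alpha 0.025 the smallest N is 292. A two-group calculation at alpha 0.025 gives 241, which is close but is neither 244 nor this design. The three-group test at 0.05 is therefore the best-fitting reading.

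**2. Power if alpha is split over two outcomes.** Evaluable N = 270 × 0.90 = 243. Omnibus power is 0.798 at alpha 0.05 and 0.710 at alpha 0.025. Restoring 0.80 at 0.025 needs 292 evaluable, or 292 / 0.90 = 324.4, so 325 randomised.

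**3. Family-wise error per trial under the global null, two-sided 0.05 per test, if any rejection counts.** For m independent tests the rate is 1 − 0.95^m. The tests here are correlated, so z-statistics were simulated with a shared control arm (correlation 0.5 between the two contrasts). The documents give no outcome or visit correlations. The values used are assumptions: 0.1 to 0.5 between outcomes, 0.5 to 0.9 between visits.

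| Tests counted | m | Independent | Simulated |
|---|---|---|---|
| One time-by-group test per outcome | 2 | 0.098 | 0.09–0.10 |
| 2 outcomes × 2 active-vs-waitlist contrasts, one visit | 4 | 0.185 | 0.16–0.17 |
| The same at post, 3 and 6 months | 12 | 0.460 | 0.26–0.39 |

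In the last row, visit correlation matters most: about 0.37–0.39 at 0.5, 0.32–0.35 at 0.7 and 0.26–0.27 at 0.9.

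**4. What the interaction test answers.** With three arms, five assessments and time as a factor, the interaction has (3 − 1) × (5 − 1) = 8 degrees of freedom. Rejecting it does not show which arm differs from waitlist, or when, so contrasts must follow. It also includes the 18-month visit.

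**5. Power of the contrasts proposed below.** Assume both active arms differ from waitlist by the same d. Then f² = 2d²/9, so d = 0.20 / √(2/9) = 0.424. Using the noncentral t with 81 evaluable per arm:

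- Pooled, 162 vs 81: noncentrality 0.424 × √(162 × 81 / 243) = 3.12; power 0.874 at alpha 0.05 and 0.805 at 0.025.
- Single arm, 81 vs 81: noncentrality 0.424 × √(81 × 81 / 162) = 2.70; power 0.765 at 0.05, 0.669 at 0.025 and 0.570 at 0.0125 (the first Holm step for two arm contrasts sharing 0.025).

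**The case against.** A reader might infer that each trial has about a one-in-three chance of a false claim because any of twelve or more unadjusted tests would count as success. The documents do not support that. The only test that Statistical methods names is one time-by-group interaction per outcome, and on that test the rate is about 10%. Nowhere does the article say that every contrast will be tested separately at every visit at 0.05. Counts that add a third contrast and the 18-month visit go further still. The caregiver contrast is listed as a secondary aim, no hypothesis compares face-to-face with virtual delivery, and the no-intervention comparison is limited to the period up to 6 months.

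The hypothesis speaks of sustained change in lifestyle and cognition together, which can be read as requiring both outcomes. Such a rule needs no alpha split. An analysis plan that is not shown may contain an adjustment, so its absence from a condensed article is no fault. Nor does sizing at 0.05 prove that error control is missing, since a fixed testing order or an omnibus gate would be sized in the same way.

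All of this stands, and it limits the size of the point. It does not remove it. The article permits several success rules with different error rates and chooses none. It places the caregiver contrast inconsistently, and its primary aim extends beyond the untreated control period. An unseen plan that split alpha would leave the stated 0.80 unmet for the omnibus test.

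**Conclusion.** The primary analysis of both trials is badly fixed: two primary outcomes, three arms and unranked follow-up horizons, with no decisive visit, contrast or success rule. If either outcome suffices, family-wise error is about 10% on the named test. It is 16–17% with two contrasts at one visit, and about 26–39% with those contrasts at the three visits up to 6 months. The last range rests on assumed correlations and on a testing practice that the article leaves open but does not state. Under a both-must-succeed rule on one test per outcome there is no inflation. With alpha split over the outcomes, omnibus power is 0.71 at 243 evaluable. The alpha of 0.05 is inferred from the exact match to 244. It would go too far to say that the trials have lost confirmatory status; the point can be settled in wording, and should be before data are seen.

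**What to change.** - **Visit.** Name the 6-month visit as the only primary time point, once confirmed to precede crossover. The clock needs reconciling: follow-up visits are counted after a 10-week programme, while Participants offers the waitlist the programme after 6 months without giving the starting point.
- **Contrast.** Make both REMINDER arms pooled versus waitlist, estimated from the mixed model, the primary contrast.
- **Outcomes.** Test the two outcomes on this contrast with Holm (0.025, then 0.05), or state that both must succeed, each at 0.05.
- **Arm contrasts.** Treat each arm versus waitlist, and active arm versus active arm, as secondary, tested only after the pooled contrast succeeds on that outcome. If they are to be confirmatory, replace the Holm step across outcomes with a fixed 0.025 for each outcome's chain. Holm-adjust the two arm-versus-waitlist contrasts within it, and pass no alpha to the other outcome until the whole chain is rejected. Otherwise the same alpha is spent twice.
- **Other visits.** Make post-intervention, 3-month and 18-month results secondary, and label 18 months as after crossover.

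**Cost.** Wording, with no added participants. Pooled power is about 0.80 at alpha 0.025, if d = 0.42 holds equally in both arms; unequal effects would change this. Under a both-must-succeed rule, power is 0.874 per outcome at 0.05 and 0.874² = 0.76 for both if the outcomes are independent and share that effect. Single-arm power falls from 0.765 at 0.05 to 0.67 at 0.025, and to 0.57 at the first Holm step when two arm contrasts share that 0.025.

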##### Secondary outcomes

The secondary outcome, assessed at baseline, post-intervention, and at 3-, 6-, and 18- months follow-up, will include:

*Specific cognitive functions* – individual cognitive measures that contribute to the primary cogniticve composite will also be analyzed separately to examine specific domans. These include:Global Cognition (Addenbrooke’s Cognitive Examination – Revised [58]); Episodic memory (Word List) [54]; Verbal Initiative (Letters P, M, R and Categories Animals Fluency) [55]; Executive Function (Behavior Rating Inventory of Executive Functions- Adults (BRIEF-A) [52]; Working Memory (Weschler Adult Intelligence Scale (WAIS) – Digit Span Task) [59].*Perceived and performance-based functional status*:Adults and Older Adults Functional Assessment Inventory (IAFAI) [60]; University of California San Diego Performance-Based Skills Assessment (UPSA Brief) [61]. *Psychosocial/Mental Health indicators*:Geriatric Depression Scale (GDS-30) [62]; World Health Organization Quality of Life (WHOQOL-OLD 7) [63]; Lubben’s Brief Social Network Scale [64]; Psychological change (Clinical Outcome Routine Evaluation) [65]; Motivation (Motivation to Change Lifestyle and Health Behaviour for Dementia Risk Reduction (MCLHB-DRR) [66].*Biological markers of neurodegeneration (assessed at baseline, post-intervention): *Currently, the most robust blood-based biomarker is the neuronal cytoplasmic protein Neurofilament light chain (NfL). NfL is a sensitive but unspecific marker of axonal injury, with potential ability to rule-in or rule-out neurodegeneration and to assess its progression rate [67]. Therefore, the value of baseline and/or longitudinal measurements of blood NfL in predicting the course of cognitive decline has been verified in different neurodegenerative dementias, and in cognitively normal individuals [68]. Importantly, since blood NfL can detect axonal damage that has occurred in the last 3 months, it has also been used as an indicator of the treatment efficacy of disease-modifying treatments [69]. Other recognized important markers are neuroinflammation and cerebrovascular function alterations and/or blood-brain barrier (BBB) damage. Glial fibrillary acidic protein (GFAP), an intermediate filament protein mainly expressed in astrocytes of the central nervous system and soluble platelet-derived growth factor receptor-β (sPDGFRβ) a marker of BBB-associated capillary mural cell pericyte, respectively, are good candidates [70]. Such markers have also recently shown potential as early surrogates of cognitive dysfunction [71–73]. We will assess the levels of blood NfL, GFAP and sPDGFRβ in a subset of the study population (33% in all study arms) before and after the intervention period. Blood samples will be collected into serum separation tubes, centrifuged at 1500 g, 4^o^C for 10 min. Serum will be separated, aliquoted and frozen at –80^o^C in the same day of collection. Serum NfL and GFAP will be quantified simultaneously using the SiMoA (Single Molecule Array) Neuro-2Plex B multiplex kit in an SR-X platform (Quanterix, USA). Serum sPDGFRβ levels will be determined separately using an already described ELISA kit.*Diagnostic transitions in MCI:*
Conversion from MCI to dementia across the 18-month follow-up, assessed via clinical evaluation and standardized cognitive assessments (e.g., ACE-R, MMSE, clinical interview). This outcome will allow examination of whether participation in REMINDER alone or REMINDER with caregiver support delays progression compared to the waiting list control.

**Table 2 Tab2:** *Measures*,* psychometric properties*,* and timepoints of assessment*

Construct and measure	Scoring	Criteria/Psychometric properties	Timepoint
Demographic characteristics			
Age, gender, education level, professional status, marital status	—	—	Screening
Clinical characteristics			
Presence of medical diagnosis, actual medication, sensory issues, mobility deficits, use of substances, previous issues and hospitalization, and Lifestyle for Brain Health (LIBRA) score [51]	LIBRA score: range from − 5.9 to 12.7	LIBRA score: higher = more risk	Screening
Primary Outcome			
* Cognitive function composite*			
Mini-mental State Examination (MMSE)	Total 0–30	Higher scores indicating better functioning	Baseline, post, 3, 6, and 18-month follow-up
Word List (WMS-III)	Sum of recalled words	Internal consistency 0.67 to 0.90 (median = 0.83)	Baseline, post, 3, 6, and 18-month follow-up
Verbal Fluency (letters and animals)	Number of correct words in 60s	Excellent reliability: α = 0.89; ICC = 0.996	Baseline, post, 3, 6, and 18-month follow-up
Trail Part B	Time to completion (sec)	Higher times = worse performance	Baseline, post, 3, 6, and 18-month follow-up
* Health lifestyle behaviors*			
Healthy Lifestyle Assessment Toolkit (HLAT)	Traffic light rating system for 8 lifestyle components: low risk (green), moderate risk (yellow), relevant risk (orange)	—	Baseline, post, 3, 6, and 18-month follow-up
Secondary outcome			
* Specific cognitive functions*:			
Addenbrooke’s Cognitive Examination – Revised (ACE-R)	Total 0–100 (with 5 subdomains)	Higher scores indicating better functioning; Excellent internal consistency (Cronbach’s α = 0.95)	Baseline, post, 3, 6, and 18-month follow-up
Behavior Rating Inventory of Executive Functions - Adults (BRIEF-A)	3-point Likert scale (1 = Never; 2 = Sometimes; 3 = Often), frequency of behaviors in the past month	Indexes and Global Executive Composite: α = ≥0.90 (very good); Scales: α = 0.70–0.80.70.80 (acceptable) or α = ≥0.80 (good)	Baseline, post, 3, 6, and 18-month follow-up
Digit Span Task - Weschler Adult Intelligence Scale (WAIS)	Total correct sequences: Forward (max = 16); Backward (max = 14); Digit memory total (max = 30)	—	Baseline, post, 3, 6, and 18-month follow-up
*Perceived and performance-based functional status*:			
Adults and Older Adults Functional Assessment Inventory (IAFAI)	50 items (0 = no functional limitation, 1 = functional limitation)	Global and domain-specific functional limitations (physical, cognitive, emotional)	Baseline, post, 3, 6, and 18-month follow-up
University of California San Diego Performance-Based Skills Assessment (UPSA Brief)	Performance score 0–100	Adequate internal consistency α = 0.86	Baseline, post, 3, 6, and 18-month follow-up
* Psychosocial/Mental health indicators*:			
Geriatric Depression Scale (GDS-30)	Sum of 30 dichotomous items (0–30)	Excellent reliability: α = 0.91; inter-rater Kappa = 0.87; good validity	Baseline, post, 3, 6, and 18-month follow-up
World Health Organization Quality of Life (WHOQOL-OLD 7)	Domain scores 8–40	Higher = better quality of life	Baseline, post, 3, 6, and 18-month follow-up
Lubben’s Brief Social Network Scale	Total scores range from 0 to 30, with higher scores indicating stronger social networks.	Higher = stronger social networks. Adequate internal consistency (Cronbach’s α = 0.80).	Baseline, post, 3, 6, and 18-month follow-up
Psychological change (Clinical Outcome Routine Evaluation)	0–4 Likert scale per item (0 = Never, 4 = Almost always), reflecting experiences in the past week	Excellent internal consistency: α = 0.94	Baseline, post, 3, 6, and 18-month follow-up
Motivation (Motivation to Change Lifestyle and Health Behaviour for Dementia Risk Reduction (MCLHB-DRR)	27 items on 7 subscales (Health Belief Model)	Moderate-to-high internal reliability: α = 0.608–0.864; test-retest reliability: α = 0.552–0.776	Baseline, post, 3, 6, and 18-month follow-up
* Biological markers of neurodegeneration*			
NfL	Pg/mL (normal expected range within 5.0–50.0 pg/ml in older adults)	Higher levels indicate increased axonal loss	Baseline, post-intervention
GFAP	Pg/mL (normal expected range within 50–300 pg/ml in older adults)	Higer leves indicate increased neuroinflammation	Baseline, post-intervention
sPDGFRβ	Pg/mL	Higher levels indicate impaired blood-brain barrier funcion	Baseline, post-intervention
Exploratory outcome (MCI subgroup)			
* Diagnostic transitions*	Conversion from MCI to dementia	Assessed via clinical evaluation, standardized cognitive assessments (ACE-R, MMSE, clinical interview).	Baseline, post, 3, 6, and 18-month follow-up

#### Participants

This study follows a randomized, waitlist-controlled design. Eligible participants will be invited to complete the baseline assessment. Recruitment will target individuals presenting modifiable dementia risk factors, as well as caregivers/relatives of MCI patients, who will be included in a dedicated experimental arm of the Clinical Trial. Following baseline assessment, participants will be randomly assigned to one of the study arms: *Community Trial –* REMINDER face-to-face, REMINDER virtual, or Waitlist Control (Fig. 2, trial flowchart); *Clinical Trial –* REMINDER intervention alone, REMINDER plus caregiver support, or Waitlist Control (Fig. 3, trial flowchart). A researcher blind to the assessment procedure will conduct randomization, and then all participants will be informed about their assigned condition. Waitlist participants will be offered the REMINDER intervention after 6 months, while all participants will be followed for 18 months post-intervention (24 months total).

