#### Hypotheses

We hypothesize that REMINDER participants will exhibit significant and sustained positive changes in lifestyle behaviors and global cognition, compared to the waitlist control group. For a subset of MCI participants, we will offer an additional condition involving the patient’s partner’s participation in REMINDER. We hypothesize that this complementary support (REMINDER4Carers) will lead to greater improvement in the primary outcome compared to REMINDER alone, according with evidence highlighting the role of care partners in behavior change interventions [22, 24]. We anticipate positive impacts in secondary psychosocial and cognitive aims as well. Additionally, in the MCI subgroup, we hypothesize that participation in REMINDER (with or without care partner involvement) will be associated with a lower rate of diagnostic transition to dementia across the 18-month follow-up.

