The REMINDER intervention combines 20 group sessions (with an approximate length of 60–75 min) twice weekly over 10 weeks. To ensure cultural relevance and engagement, sessions integrate Portuguese-specific elements, such as song lyrics from the Festival da Canção, references to the 25th of April revolution, and discussion prompts related to participants’ autobiographical experiences. The content of sessions will integrate brain health psychoeducation, cognitive training, the practice of compensatory memory aids, personally meaningful goals management training, and stress management techniques (see Fig. 1 for the conceptual model of the REMINDER intervention and Table 1 for detailed session contents). Specifically, a set of contents and structures were designed to address existing gaps in the literature. Namely, to overcome low adherence, the program includes interactive and personalized sessions, including strategies like goal setting and mindfulness drawing from previous work with these populations [43, 46], as well as motivational strategies (motivational interviewing, positive reinforcement, and progress tracking) to encourage adherence. In addition, to target specifically the psychosocial risk factors (stress, social isolation, depression, among others) [47], we incorporated stress management techniques based on scripts from compassion-based therapies as well as relaxation techniques [48, 49], social interaction and support and emotion regulation strategies (e.g. attention deployment, positive cognitive reappraisal, reframing speech training). Believing that merging the brain, these behavioral strategies in a dementia risk reduction program will foster individuals’ mental health and build their capacity to draw on improved psychological and cognitive reserve to prevent and cope with remaining risk factors.

A manualized protocol was developed to provide standardized elements and detailed guidelines for program delivery. Health professionals (psychologists, neuropsychologists) delivering the intervention will receive training using the manual before to implementing REMINDER. Postdoctoral-level clinical psychologists from the research team members will lead the interventions in both delivery modes (face-to-face and virtual). To minimize bias, the professionals delivering the program will be counterbalanced across the two delivery methods.

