##### Waiting list control groups

A waitlist control design was selected to ensure provision of the intervention to all participants while allowing comparison with a no-intervention condition over the 6-months follow-up period. After the 6-month follow-up period, participants in the control group will receive the REMINDER intervention, which can be attended either in-person or via videoconferencing, depending on participants’ preference and logistical considerations. Participants’ engagement in other active interventions during the 6-month study period will be monitored through regular follow-up contacts.

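### The stated follow-up figures contradict each other and the waitlist's time origin for the 18-month visit is not fixed, so the time at risk for conversion to dementia may differ between arms

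*Protocol article*

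**What the plan says.** All places are in the protocol article.

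- **Participants** sets the follow-up for everyone: "Waitlist participants will be offered the REMINDER intervention after 6 months, while all participants will be followed for 18 months post-intervention (24 months total").
- **Waiting list control groups** places the waitlist's programme later: "After the 6-month follow-up period, participants in the control group will receive the REMINDER intervention". The same section describes the design as "allowing comparison with a no-intervention condition over the 6-months follow-up period".
- **The REMINDER intervention** gives the programme length: "The REMINDER intervention combines 20 group sessions (with an approximate length of 60–75 min) twice weekly over 10 weeks".
- **Secondary outcomes** defines the endpoint as "Conversion from MCI to dementia across the 18-month follow-up" and asks whether REMINDER, alone or with caregiver support, "delays progression compared to the waiting list control". **Hypotheses** expects that taking part "will be associated with a lower rate of diagnostic transition to dementia across the 18-month follow-up".
- **Outcomes** and **Table 2** give one visit list for all participants: baseline, post, and 3, 6 and 18 months. They give no separate waitlist timing.
- **Statistical methods** assigns Markov models to diagnostic transitions and does not say whether time is actual elapsed time or visit number.

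**The concern.** The sentence in Participants does two things at once. It gives the waitlist a later intervention, and it says that every participant is followed for the same period after the intervention. If that means each arm's own intervention, the waitlist's last diagnostic assessment comes months later after randomisation than that of the active arms. The total given in the same sentence would instead put all participants on the same length of follow-up.

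This matters most for conversion to dementia. Cumulative conversion grows with time at risk, so an arm observed for longer shows more conversions even if the programme does nothing. The excess would fall in the waitlist, which is the direction of the stated hypothesis. This is the trial's only outcome based on a clinical diagnosis of dementia.

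**Working it through.** **Inputs.** The programme lasts 10 weeks (The REMINDER intervention). The wait is 6 months (Participants; Waiting list control groups). Follow-up is 18 months post-intervention, with 24 months in total (Participants). Annual conversion from MCI is 10–15% (Background and rationale; a background figure for Alzheimer's disease, used here as the rate in every arm). There are 90 patients per arm (Sample size). The gap between randomisation and the start of the programme is taken as negligible.

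**Step 1: try to reproduce the stated 24 months.** 10 weeks = 10 × 7 / 30.4375 = 2.3 months.

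- Active arms: 2.3 + 18 = 20.3 months.
- Waitlist on its own programme, wait of 6 months from randomisation: 6 + 2.3 + 18 = 26.3 months.
- Waitlist on its own programme, wait ending at the 6-month visit after the post assessment: 2.3 + 6 + 2.3 + 18 = 28.6 months.
- 24 months arises only as 6 + 18. This adds the waitlist delay and leaves out the programme.

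The stated total is therefore not reproduced for either group when time is counted from the end of the programme.

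**Step 2: extra time at risk on the literal reading.** 26.3 − 20.3 = 6.0 months, or 28.6 − 20.3 = 8.3 months. Relative to 20.3 months, that is 30% or 41% longer.

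**Step 3: conversion with no treatment effect.** With a constant hazard and annual rate r, the risk by month t is 1 − (1 − r)^(t/12). For example, 1 − 0.90^(20.3/12) = 16.3% and 1 − 0.90^(26.3/12) = 20.6%.

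| Annual rate | Active, 20.3 mo | Waitlist, 26.3 mo | Difference | Waitlist, 28.6 mo | Difference |
|---|---|---|---|---|---|
| 10% | 16.3% | 20.6% | 4.3 points | 22.2% | 5.9 points |
| 15% | 24.0% | 30.0% | 5.9 points | 32.1% | 8.1 points |

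Differences are taken before rounding. Per 90 patients they amount to about 4 to 7 extra waitlist conversions. The apparent risk ratio is 0.79–0.80 at 26.3 months and 0.73–0.75 at 28.6 months.

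**Step 4: the same calculation on one clock.** At a common 20.3 months, every arm has 16.3% (10% per year) or 24.0% (15% per year). At a common 24 months, every arm has 19.0% or 27.8%. The null difference is zero in both cases.

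**Step 5: does the planned model remove it?** A Markov model fed with actual elapsed time accounts for the unequal intervals and would largely remove the bias. One indexed by visit label would not. From the 6-month visit (month 8.3 on the active calendar) to the 18-month visit is 12 months in the active arms. In a waitlist seen last at month 26.3 or 28.6, the same labelled step lasts 18 or 20.3 months. Statistical methods does not say which form is meant.

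**The case against.** The strongest reply is that all arms share one calendar. Outcomes and Table 2 give a single visit list. The untreated comparison also requires the waitlist's post, 3-month and 6-month visits to occur before its own programme, hence on the active arms' calendar. The 18-month visit belongs to the same list, and the total in Participants is stated for everyone. The Clinical Trial flowchart (Fig. 3) is not shown and may settle the matter. This stands as a plausible reading, and under it the bias is absent. It does not rescue the sentence: on that calendar the last visit is at about 20.3 months, not 24.

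A reader might infer that the trial will make REMINDER appear to prevent dementia when it has no effect. The documents do not support that as a fact. No section says that the waitlist's clock restarts for its last visit, and the bias needs both that reading and an analysis that ignores elapsed time.

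A reader might also convert the false difference into an inflated chance of a significant result. Any such figure assumes a crude two-proportion test, which the article does not assign to this outcome.

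Two further points stand. The abstract, Objectives and Table 2 label conversion exploratory, and the sample size does not rest on it, although the Secondary outcomes section also lists it and Hypotheses gives it a direction. On a common clock the waitlist's later receipt of REMINDER pulls any true difference toward zero. At an assumed hazard ratio of 0.7, a true difference of 4.6–6.5 points at 20.3 months would be seen as only 1.4–2.7 points. That is a separate issue, and aligning the clocks does not remove it.

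**Conclusion.** The point holds as a contradiction in the stated follow-up and an unfixed time origin for the waitlist. Eighteen months after the intervention and 24 months in total cannot both be true for all participants: the active arms reach about 20.3 months, and a waitlist timed from its own programme about 26.3 or 28.6.

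The consequence for conversion is conditional. If each arm is timed from its own intervention and crude proportions (or visit-indexed transitions) are compared, the null difference favours REMINDER by about 4–6 points at 26.3 months, and by up to about 8 points at 28.6. If all arms share one calendar, it is zero.

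The sizes rest on a constant hazard and on the article's 10–15% annual figure applied equally to all arms. The direction needs only a positive hazard. Because the outcome is mostly labelled exploratory, the primary conclusions are not at stake, but the correction should be made.

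**What to change.** Reconcile Objectives, Waiting list control groups, Outcomes, Secondary outcomes, Table 2 and Participants so that:

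1. The 18-month visit and the conversion window have one origin, randomisation, and one common horizon in all three Clinical Trial arms. The sponsor should state which horizon is meant; about 20.3 or 24 months would each equalise time at risk.
2. The total follow-up in Participants is restated to match that horizon.
3. Conversion is analysed by actual time since randomisation, with the Markov model specified accordingly. Conversions after the common horizon are left out of the between-arm comparison.

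The end of data collection in the Recruitment section should be checked at the same time. January 2026 to about mid-2027 is roughly 18 months, which is shorter than any of these horizons for even the first participant.

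The cost is wording, the visit calendar and the time variable in one model, with no extra patients. The small downside is that a waitlist visit timed from its own programme, if wanted, would not count in the between-arm comparison.
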